## Abstract

**Background:**

Thyroid dysfunction is associated with cognitive impairment, mood disturbance, and postnatal depression. Sufficient thyroid hormone synthesis requires adequate intake of iodine, selenium, and iron. Iodine deficiency was historically a problem for New Zealand, and initiatives were introduced to overcome the problem: (1) mandatory fortification of all bread (except organic) with iodized salt (2009) and (2) provision of subsidized iodine supplements for pregnant and breastfeeding women (2010). Subsequent to these initiatives, most adults and children have adequate iodine status; however, status among breastfeeding women and their infants remains unclear. This paper outlines the methodology of the Mother and Infant Nutrition Investigation (MINI) study: an observational longitudinal cohort study of breastfeeding women and their infants.

**Objective:**

This study will determine (1) women’s iodine intake and status among supplement users and nonusers; (2) women’s intake and status of iodine, selenium, and iron relating to thyroid function; (3) associations between women’s selenium status, thyroid function, and postnatal depression; (4) infants’ iodine and selenium status relating to first year neurodevelopment.

**Methods:**

Breastfeeding women aged over 16 years with a healthy term singleton infant were recruited from Manawatu, New Zealand. Participants attended study visits 3, 6, and 12 months postpartum. Maternal questionnaires investigated supplement use before and after birth, iodine knowledge, and demographic information. Dietary assessment and urine, blood, and breast milk samples were taken to measure iodine, selenium, and iron intake/status. The Edinburgh Postnatal Depression Scale was used repeatedly to screen for postnatal depression. Thyroid hormones (free triiodothyronine, free thyroxine, thyroid stimulating hormone, thyroglobulin, antithyroglobulin antibodies, and antithyroid peroxidase) were measured in blood samples, and thyroid gland volume was measured by ultrasound at 6 months postpartum. Infant iodine and selenium concentrations were determined in urine. The Ages and Stages Questionnaire was used to assess infant development at 4, 8, and 12 months.

**Results:**

Data collection was completed. Biological samples analysis, excluding nail clippings, is complete. Data analysis and presentation of the results will be available after 2020.

**Conclusions:**

This study will provide data on the current iodine status of breastfeeding women. It will also provide a greater understanding of the three essential minerals required for optimal thyroid function among breastfeeding women. The prospective longitudinal design allows opportunities to examine women’s mental health and infant neurodevelopment throughout the first year, a crucial time for both mothers and their infants.

**Trial Registration:**

Australian New Zealand Clinical Trials Registry ACTRN12615001028594; https://www.anzctr.org.au/Trial/Registration/TrialReview.aspx?id=369324

**International Registered Report Identifier (IRRID):**

DERR1-10.2196/18560

## Introduction

### Background

Postpartum women experience abnormalities in thyroid function at twice the prevalence of the general population [1]. Thyroid hormone is essential in maintaining the human body’s metabolism, temperature (thermoregulation), and psychological mood [2]. In a developing brain, thyroid hormone is responsible for adequate myelination, neuron cell maturation, and central nervous system development [3]. Optimal thyroid function relies on adequate biosynthesis of thyroid hormones, which depends on three dietary minerals: iodine, selenium, and iron [4,5]. Pregnancy increases thyroid hormone turnover; thus, women with limited thyroidal reserve or marginal iodine deficiency are at increased risk to develop thyroid dysfunction after birth [6]. This is one of the most common endocrine disorders that postpartum women experience [7].

Iodine is the major component of thyroid hormones, but it is also a regulator for the synthesis and secretion of the thyroid hormones triiodothyronine (T3) and thyroxine (T4). Selenium, as a component of the selenocysteine-containing proteins glutathione peroxidase, protects the thyroid gland from oxidative damage [5]. Selenoproteins are required to convert T4 to T3, the active form of thyroid hormone. Iron is required for heme-dependent thyroperoxidase activity, which is required for the synthesis of adequate thyroid hormone. Selenium deficiency and iron deficiency anemia may negatively affect thyroid hormone synthesis by impairing selenium- and iron-dependent enzyme activities, even if iodine status is adequate [5]. Most previous research has investigated iodine, selenium, and iron intake/status separately or a combination of any two of them among women of childbearing age [8] and postmenopausal women [9]. However, further research is needed to explore all three micronutrients together, acknowledging their close relationship in thyroid hormone synthesis.

Thyroid dysfunction is a significant health issue in New Zealand, with women diagnosed at 5 times the prevalence in men [10,11]. Concerning adequate thyroid function, iodine, selenium, and iron play important roles. In New Zealand, soils provide low levels of available iodine and selenium, resulting in low concentrations in the food supply [12], hence in the diet [13]. Iodine deficiency in early life is associated with impaired neurodevelopment [14]. Iodine deficiency was a concern in New Zealand in the early years of the 20th century, but its prevalence was mostly reduced through the introduction of iodized salt in the 1930s. However, since the 1990s, a number of studies in New Zealand have shown iodine deficiency has reemerged in adults [15], pregnant and breastfeeding women [16,17], school children [18] and breastfed infants and toddlers [19]. To improve iodine status in New Zealand, two government initiatives were introduced: mandatory iodized salt in commercially made bread products from September 2009 and the provision of iodine supplementation for all pregnant and lactating women in 2010 [20]. Although recent studies suggested that adults [21,22] and children [23] in New Zealand may now have adequate iodine intake/status, both pregnant and breastfeeding women remain deficient. A pilot study of a small sample of self-selected highly educated pregnant and breastfeeding women assessed urinary iodine excretion, breast milk iodine concentration, and blood thyroglobulin and suggested iodine deficiency [24]. There is a need for a more robust investigation into the iodine status of postpartum women and their infants from a wide range of socioeconomic backgrounds.

Low selenium status in New Zealand has been partially reversed by increased consumption of imported flour from Australia (which generally has higher selenium concentrations than flour produced in New Zealand) [25,26]. In addition, both pregnant and breastfeeding women have an increased requirement for dietary selenium due to the demands from the fetus and breastfed infants. Previous research, which investigated selenium status among postpartum women and their infants in New Zealand 20 years ago [27], measured urinary selenium excretion and plasma selenium and indicated that such women were at risk of selenium deficiency. To our knowledge only one small study of breastfeeding women, by our research group, assessed dietary selenium, urinary selenium excretion, and breast milk selenium concentration and suggested selenium inadequacy was still a concern [28]. There remains a lack of research investigating selenium status among postpartum women and their infants.

Health professionals closely monitor the iron status of women during pregnancy. However, after birth, management of iron status can be inconsistent. Results from a UK multicenter study reported only 50% of postpartum women had hemoglobin levels checked after delivery (with 30% of those women confirmed as anemic), while the overall iron stores of participating women remained unexamined [29]. Generally, postpartum women’s iron status recovers as a consequence of cessation of menstrual bleeding since conception or a minimal secretion of iron via breast milk if breastfeeding [30]. However, if women have suffered iron deficiency before and/or during pregnancy and/or have experienced significant blood loss during the birth, their iron status may not reach optimal levels even if an intervention subsequently occurs. A New Zealand study of 186 women found 77% of women were not tested for hemoglobin levels after birth. Further, out of those most at risk (with low iron status during late pregnancy and high blood loss, exceeding 500 mL, during birth), few women were then retested for their iron status after 10 days postpartum [31]. Iron status of postpartum women remains largely underreported.

Moreover, low serum selenium has been identified as an independent risk factor for depression, [32] and selenium supplementation has been observed to reduce postnatal depression [33]. Postnatal depression is one of the main disorders women experience postnatally, its onset being timed at 6 weeks to 6 months after birth. Most women will recover from postpartum depression, though approximately one-quarter of affected women report being depressed when their infant reaches their first birthday [34]. Using the measured criteria of postnatal depression on the Edinburgh Postnatal Depression Scale (EPDS), the prevalence of postnatal depression in New Zealand was about 8% in 1994 and 16% in 2006. In the 2015 New Mothers’ Mental Health Survey [35], the prevalence was 14% and is now recorded as the most common disorder for mothers in their first year after childbirth [36].

Of additional concern, mothers are often reluctant or unable to seek help when they experience symptoms of postnatal depression [35]. Such underdiagnosed and untreated mental health conditions affect both the mother and their children’s ongoing cognitive, emotional, and behavioral development [37]. Despite other social and psychological etiology of depression, potential links between micronutrient status, thyroid hormone, and the risk of postpartum depression need to be further explored. This may help develop new preventive approaches to lowering the risks of postpartum depression.

### Study Objectives

The study’s primary outcomes include (1) investigating breastfeeding women’s iodine intake and status among supplement users and nonusers following the implementation of two government initiatives to improve iodine status; (2) examining maternal iodine, selenium, and iron intake status; and (3) exploring iodine, selenium, and iron status in maternal thyroid function.

In addition, the study provides preliminary data on possible associations between women’s selenium status, thyroid function, and postnatal depression over a 1-year period and infants’ iodine and selenium status in relation to neurodevelopment during their first year of life. Ultimately, this research will inform a future larger study of potential variables impacting maternal thyroid function and the risk of postnatal depression, together with early infant neurodevelopment.

## Methods

### Study Design and Overview

The Mother and Infant Nutrition Investigation (MINI) study is an observational longitudinal cohort study spanning the first year postpartum. It was approved by the Health and Disability Ethics Committee (15/NTA/172) in December 2015. The study’s ethics approval was registered with the Royal New Zealand Plunket Ethics Committee in June 2016. The MidCentral District Health Board in New Zealand also approved the study. The study was registered with the Australian New Zealand Clinical Trials Registry [ACTRN12615001028594].

The study is being conducted in the Human Nutrition Research Unit at Massey University, Palmerston North, New Zealand. The first study visit for participants is at approximately 3 months postpartum, and follow-up assessments take place at 6 months and 12 months postpartum (Multimedia Appendix 1).

### Selection Criteria

The target population for the study was healthy breastfeeding women aged over 16 years who had birthed a healthy term singleton infant 3 months prior. Women were excluded if they developed significant health problems, such as metabolic disease or cancer. Women were excluded if they had been diagnosed or treated at any time for hyperthyroidism or hypothyroidism. Participants were required to live within or near the local Palmerston North area and be able to attend Massey University for scheduled study visits. Women of any ethnic and socioeconomic status were eligible.

### Recruitment and Participation

Posters to promote the study were placed at selected sites (general practitioner surgeries, midwifery clinics, pharmacies, antenatal classes, ultrasound clinics, maternal wards in hospitals, local community playgroups, and early childhood centers, etc). Local newspapers and social media sites were used to publicize the study. Local midwives, childbirth educators, and lactation consultants were asked to raise awareness of the MINI study to their clients. An effort was made to recruit women from a wide range of socioeconomic backgrounds and ethnic groups, including Maori, Pacific Islanders, and Asian women. Potential participants responded by recording an expression of interest online or via telephone or email. Prospective participants were provided with a study information sheet. Interested participants then completed a screening questionnaire to ensure eligibility. Written informed consent was obtained from all participants before their enrollment in the study. Mothers also gave written consent to their infants’ participation in the study. After providing informed consent, participants were assigned a unique identifier code and scheduled for their first study visit.

### Sample Size Calculation

The main outcome measure was iodine excreted per day, and the sample size was calculated using G*Power 3.1 (Heinrich Heine University) based on data (mean and standard deviation) from a preliminary study of breastfeeding women [24]. Calculation used 1-way analysis of variance with two groups (95% power, 𝛼=.05, 2-tailed) and three repeat measures; 80 participants were needed, using expected mean daily urine iodine concentrations of 140 and 100 µg/d for iodine supplement users and nonusers, respectively, and a standard deviation of 60.

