### Statistical Analysis

Statistical analysis will be performed using SPSS Statistics version 23. The Shapiro-Wilk test will be used to test for data normality. Nonparametric data will be expressed as median (25th, 75th percentile), and parametric data will be expressed as mean and standard deviation. Bivariate correlations will be tested using the nonparametric Spearman 𝜌 correlation coefficient. Repeated-measures analysis of variance will be used to calculate continuous variables between groups. Nonparametric Mann-Whitney *U* test (2-tailed) will be used to examine iodine intake and status between supplement users and nonusers. Multiple regression models analysis will be used to determine the associations between iodine, selenium, iron status, and thyroid function, as well as considering confounding factors. Multivariate analysis will be used to examine possible associations between women’s selenium status, thyroid function, and postnatal depression and infant first year neurodevelopment.

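### The user/nonuser comparison was sized on a three-visit ANOVA but is assigned to a Mann-Whitney U test, and the article does not say which analysis tests the main outcome

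*Protocol article*

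**What the plan says.** In the Protocol article, the Sample Size Calculation section defines the target: "The main outcome measure was iodine excreted per day". On the method it says "Calculation used 1-way analysis of variance with two groups", at 95% power and a two-tailed alpha of 0.05. It continues: "three repeat measures; 80 participants were needed, using expected mean daily urine iodine concentrations of 140 and 100" µg/d for users and nonusers respectively, "and a standard deviation of 60".

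The Statistical Analysis section has two relevant sentences, one after the other. The first plans repeated-measures analysis of variance for continuous variables between groups, without saying which variables or which groups. The second says that a Mann-Whitney U "test (2-tailed) will be used to examine iodine intake and status between supplement users and nonusers". It is the only sentence in that section that mentions supplement users and nonusers. Nothing says how the three visits would enter the Mann-Whitney test.

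Tables 1 and 2 show maternal spot urine, with iodine and creatinine, at all three visits. Iodine intake is measured less often: the 4-day diary at visit 1, and the iodine/selenium food frequency questionnaire at visits 1 and 3. The Results section reports 91 mother-infant pairs enrolled.

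**The concern.** Investigating iodine intake and status in users and nonusers is listed first among the study's primary aims, and it is the only comparison for which a sample size is given. The calculation takes credit for three measurements per woman. A Mann-Whitney test compares two independent samples and has no within-woman term, so it gains from the repeats only if they are first reduced to one value per woman. If the sentence that names users and nonusers is followed at each visit separately, that gain is lost.

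What is at stake is how a non-significant result would be read. A reader would set it against 95% power, although the test actually run may have had noticeably less. With two different tests covering the same contrast and neither called primary, the choice could also be made after both results are known.

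**Working it through.** **Inputs.** From the Sample Size Calculation section: means 140 and 100, SD 60, two-sided alpha 0.05, power 95%, m = 3 repeats, N = 80. From the Results section: 91 enrolled. Assumed here, because the article does not give them: within-woman correlation rho (0.5, with a range) and equal numbers of users and nonusers. Supplement use is observed and not allocated, so the real split may differ.

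**Effect size.** d = (140 − 100)/60 = 0.667. For two equal groups f = d/2 = 20/60 = 0.333.

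**Step 1: reproduce the plan's figure.** For the between-groups effect in a repeated-measures ANOVA, power comes from a noncentral F(1, N − 2) with lambda = N·f²·m/(1 + (m − 1)·rho).

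With N = 80 and rho = 0.5, lambda = 80 × 0.1111 × 3/2 = 13.33 and power = 0.950. N = 78 gives 0.945. The stated 80 therefore reproduces.

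| rho | N for 95% power | power at N = 80 |
|---|---|---|
| 0.3 | 66 | 0.98 |
| 0.4 | 74 | 0.97 |
| 0.5 | 80 | 0.950 |
| 0.6 | 88 | 0.93 |
| 0.7 | 96 | 0.91 |

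Eighty women give at least 95% power for any rho up to 0.5. With 91 women and rho = 0.5, power is 0.97.

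**Step 2: take the repeats away.** With m = 1 and N = 80, lambda = 80 × 0.1111 = 8.89, and the ANOVA or t test has power 0.84. It needs 120 women for 95%.

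**Step 3: Mann-Whitney at one visit, normal data.** The effective group size is 40 × 3/π = 38.2, so the noncentrality is 0.667 × √(38.2/2) = 2.91. Power is 0.82, and a simulation of 10,000 runs gives 0.81. About 63 women per group (126 in total) would be needed for 95%. At the enrolled number, split 46/45, power is 0.86 to 0.87.

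**Step 4: same test under other readings, 80 women split 40/40 (simulation).**
- One visit, lognormal data with the same means and SD: 0.94.
- Each woman's three-visit mean, normal data, rho = 0.5. The SD of the mean is 60 × √((1 + 2 × 0.5)/3) = 49.0, so d = 40/49.0 = 0.82. Power is about 0.94.
- Three-visit mean at rho = 0.3 and 0.7: 0.98 and 0.89.

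**Step 5: sensitivity to the split.** With 60 and 20 women, single-visit Mann-Whitney power is 0.70 for normal data and about 0.85 to 0.89 for lognormal data. The three-visit ANOVA at rho = 0.5 gives 0.88.

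**The case against.** The strongest reply is that the sized analysis is already in the plan. The sentence just before the Mann-Whitney one provides for repeated-measures ANOVA between groups, urinary iodine is continuous and measured at every visit, and users and nonusers are the only groups that the calculation names. Mann-Whitney also has a natural use for intake, which is not measured at all visits. This stands to the extent that the powered analysis cannot be called absent. It does not settle the matter, because that sentence is generic, while the next one assigns status as well as intake, by user group, to Mann-Whitney.

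A reader might infer that the plan cannot deliver its stated power. The documents do not support that. They do not say that Mann-Whitney will be run one visit at a time. A per-woman mean recovers nearly all the power at rho = 0.5. Skewed data, which are plausible with an SD of 60 on means of 100 to 140, bring even a single-visit test to about 0.94. Enrolment also exceeded 80.

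A reader might also infer that visits will be stacked as if independent. That would inflate the type I error to about 16% at rho = 0.5, but the article does not propose it.

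Finally, the correlation, the split and the completeness of follow-up are details that a condensed article may leave to the full protocol or analysis plan. They enter here only as assumptions of the check, and their absence is not part of the point.

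**Conclusion.** The point holds as a mismatch between two sections. The main comparison is sized on one analysis, the sentence that names that comparison assigns it to another, and no primary analysis is fixed. The sample size itself is sound on its own terms: 80 women and 95% power reproduce at rho = 0.5 with equal groups.

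The size of the problem depends on the reading. A visit-by-visit Mann-Whitney test on the stated inputs, with normal data and equal groups, falls short of 95% by about 13 to 14 percentage points at 80 women and by about 8 to 9 points at 91. Under lognormal data, or with a three-visit mean at rho = 0.5, the shortfall at 80 women is about 1 point. If the repeated-measures ANOVA is the main test, there is none at rho up to 0.5. Severity is moderate: an ambiguity in the main comparison that should be closed before the data are analysed, and not a demonstrated loss of power.

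**What to change.** Reconcile the Sample Size Calculation and Statistical Analysis sections by naming one primary user/nonuser analysis of urinary iodine that uses all three visits per woman. The repeated-measures ANOVA already planned would do, once its outcome and groups are stated. A linear mixed model would serve as well. Either should be on the log scale if the data are skewed. Keep Mann-Whitney for iodine intake and for per-visit description, and say that the three visits will not be pooled as independent observations.

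If the single-visit Mann-Whitney test is kept as the main test, restate its power as about 81 to 82% for 80 women, equal groups and normal data.

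The cost is a few sentences in two paragraphs and, at most, one extra model on data already collected. No further participants or measurements are needed.

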### Outcome Measures

#### Questionnaires

At the initial visit, general baseline questions were asked about salt and supplements use, nutrition knowledge of iodine, tobacco and alcohol use, breastfeeding patterns, general health, and demographic information (including age, ethnicity, educational attainment, household size, and income). Potential changeable information including tobacco and alcohol use, breastfeeding patterns, and general health was also sought at the second and third visits.

Participants were assessed about their general health and that of their infants by online questionnaire when infants reached 6 months and 12 months of age. During the postpartum period, stress may negatively affect immunity, and the occurrence of infection symptoms can be an estimated measurement of postpartum immune function. The Carr Infection Symptom Checklist, which has been validated for use with postpartum women [38], was used to measure the symptoms of infection experienced by the mother since the birth. The Infant Symptom Checklist (which reports the frequency of symptoms of common illnesses in young infants) was used to measure the health of infants [38].

The 10-item EPDS was completed online by participating women to assess any symptoms of depression and anxiety over the previous 7 days. Women recorded severity of symptoms on a 4-point scale [39]. Specified anxiety disorders were evaluated using the EPDS-3A, a cluster of selected question items numbered 3, 4, and 5 from the original EPDS [40]. This is a validated tool to screen for probable anxiety and depression during the postpartum period. A cutoff point of 13 or above was used to define high levels of depressive symptoms [35]. Any woman whose score equaled 13 or above was advised to see her general practitioner for further evaluation as well as being provided with an information sheet containing postnatal depression services in New Zealand. Only study participants with the correct link supplied via emails could complete these questionnaires. All questions were answered in the same order. Participants could not go back to change their answers once the questionnaire was completed. Answers from incomplete questionnaires may be used for analysis.

The first year of infant neurodevelopment was assessed using a parent-completed Ages and Stages Questionnaire (ASQ) when the infant was aged 4, 8, and 12 months [41]. These questionnaires were self-administered and completed in hard copies. This screening tool uses parent observation to assess child development and behavior and records results in 5 developmental domains: communication, gross motor, fine motor, problem solving, and personal-social. There are 6 questions in each domain, with answers of yes, sometimes, or not yet. A yes indicates reaching the achievement with 10 points awarded, a sometimes indicates partial achievement with 5 points awarded, and a not yet indicates not achieved with 0 points awarded. The sum score of each domain was calculated and compared with the cutoff scores reached, which were derived empirically by subtracting 2 standard deviations from the mean for each area of development [41]. A score below the cutoff point indicates a fail on the ASQ. The questionnaires were used to assess the relationship between maternal and infant iodine and selenium status, maternal iron status, and recorded early child neurodevelopment.

